## Abstract

**Background:**

Programs for population screening of colorectal cancer (CRC) have been implemented in several countries with fecal immunochemical testing (FIT) as the preferred platform. However, the major obstacle for a feces-based testing method is the limited compliance that reduces the clinical sensitivity for detection of participants with non-symptomatic CRC. Therefore, research approaches have been initiated to develop screening concepts based on biomarkers in blood. Preliminary results show that protein, genetic, epigenetic, and metabolomic components may be valuable in blood-based screening concepts, particularly when combinations of the various components appear to lead to significant improvements.

**Objectives:**

The protocol described in this paper focuses on the validation of concepts based on biomarkers in blood in a major population screened by FIT.

**Methods:**

In Part 1, participants will be identified and included through the Danish CRC Screening Program comprising initial FIT and subsequent colonoscopy to those with a positive result. Blood samples will be collected from 8000 FIT-positive participants, who are offered subsequent colonoscopy. Findings and interventions at colonoscopy together with personal data including co-morbidity will be recorded. Blood samples and data will also be collected from 6000 arbitrarily chosen participants with negative FIT. In Part 2, blood samples and data will be collected from 30,000 FIT-negative participants three times within 4 years. The blood samples will be analyzed using various in-house and commercially available manual and automated analysis platforms.

**Results:**

We anticipate Part 1 to terminate late August 2016 and Part 2 to terminate late September 2022. The results from Parts 1 and 2 will be presented within 12 to 18 months from termination.

**Conclusions:**

The purpose of this study is to improve the efficacy of identifying participants with neoplastic bowel lesions, to identify false negative participants, to identify participants at risk of interval neoplastic lesions, to improve the compliance in screening sessions, and to establish guidelines for out-patient follow-up of at-risk participants based on combinations of blood-based biomarkers.

## Introduction

Colorectal cancer (CRC) represents the second leading cause of cancer-related death in Europe with a high social and economic impact on human health [1,2]. Population-based screening has been shown to reduce the incidence of CRC and lead to improved overall survival, presumably because the disease is diagnosed in precursor or early stages [3,4].

Direct colonoscopy is considered the gold standard for CRC screening: sensitivity and specificity are higher than 95% for diagnosing neoplastic lesions if performed by experienced colonoscopists [5]. However, the feasibility of direct colonoscopy as a screening method is challenged by capacity requirements, costs, and side-effects such as bleeding, arrhythmia episodes, and bowel perforation. Consequently, a focus has been on the development of methods to identify participants having increased risk of CRC in order to selectively offer colonoscopy. At present, fecal immunochemical testing (FIT) is probably the optimal test for identifying high-risk participants as it outperforms other fecal-based tests when it comes to usability, sensitivity, compliance, and costs [6]. FIT has some limitations, however; the positive predictive value of FIT for diagnosing CRC is in the range of 6% to 10% [7-9], and consequently greater than 10 colonoscopies have to be performed in order to diagnose one case of CRC. An additional drawback is the risk of interval cancer - CRC diagnosed in the timeframe between screening rounds mostly due to false negative FIT results. The predominant challenge is the association with low patient compliance in the range of 33% to 64% which reduces the clinical sensitivity significantly [9,10], resulting in a large proportion of undiagnosed CRC among participants who have not taken the test in addition to participants with a false negative result of FIT. An urgent need has therefore emerged to develop improved methods for early detection of CRC with high performance regarding sensitivity and improved compliance.

Major efforts have been invested in research making use of biological markers in blood to identify high-risk participants who should be offered subsequent colonoscopy. A blood sample is easy to retrieve and is far more acceptable for a screening population consisting mostly of healthy participants compared with fecal samples required for FIT [11,12]. Blood-based biological markers of interest are a heterogeneous group consisting of various proteins, nucleosomes, transcriptomes, metabolomes, circulating tumor-derived DNA, and microRNAs having shown association with early stages of CRC [13-17]. In particular, a combination of biomarkers, which results in a complementing performance, has shown promising results [13,14,18-21].

It has been shown that the presence of various benign diseases including diabetes, liver fibrosis, asthma, and chronic obstructive lung disease may cause elevated levels of specific biological protein and methylated gene markers associated with CRC [13]. Such associations with epigenetics, transcriptomics, and metabolomics have not yet been evaluated, but particular results will be presented shortly. Statistical and mathematical analyses have shown that such associations may be taken into account and thereby blood-based biomarkers may still identify participants at risk of CRC [17]. In addition, an individualized risk assessment evaluation (RAE) can be performed in order to identify participants with high risk of having CRC. This is done by combining subject-based data (ie, age, gender, body mass index, the presence of other specific diseases, etc) with the results of the biological marker analyses [17]. The mathematical model of the RAE is dynamic and can be improved by adapting data according to new findings of potential biological markers or other individualized data found to be relevant for the risk of having CRC.

At present, the established RAE model is undergoing validation in a major multicenter study (the Endoscopy II Project) [22]. In collaboration with academic and industrial partners various genetic and epigenetic molecules, proteins, and metabolites are presently being analyzed in collected blood samples. Based on results achieved from that study, a specific profile will be constructed consisting of the combination of analyzed biomarkers selected according to the statistical association with early stage CRC and high-risk adenomas. This panel will then be used to validate the designed RAE model.

The population of the Endoscopy II Project consists of participants undergoing diagnostic colonoscopy due to symptoms attributable to CRC; hence the validated RAE model found in the Endoscopy II Project is only applicable to such populations. However, if the RAE is to be implemented in future programs the screening population will comprise asymptomatic participants. Hence, it is an absolute requirement that the RAE model is validated in an asymptomatic population. The aim of the present Endoscopy III Project is to validate the RAE model in a population consisting of participants of the Danish screening program.

## Methods

### Part 1

Eligible participants are identified through the Danish CRC Screening Program that is based on an outreach FIT and subsequent offer of colonoscopy to participants with positive test results. The screening program was initiated in March 2014 and is offered to Danish citizens of 50 to 74 years of age. Screening is to be repeated every second year after the initial implementation period of 4 years. The study population consists of two sub-groups, in accordance with the FIT result; FIT-positive participants (hemoglobin [hgb] ≥ 100 ng/mL; OC-Sensor platform) and FIT-negative participants (hgb < 100 ng/mL: OC-Sensor platform).

Participants undergoing subsequent screening colonoscopies at Amager/Hvidovre, Bispebjerg, Herlev, Herning, Hillerød, Holstebro, Horsens, Randers, Silkeborg, and Viborg hospitals will be invited to participate in the project. The result of the positive FIT and booking information for colonoscopy will be forwarded to the screening participants. Simultaneously, an electronic letter with study information and an invitation to attend the Endoscopy III Project will be forwarded to the participants. The inclusion was initiated May 2014 and is planned to terminate by late August 2016. The scheduled number of participating FIT positive participants is set to 8000.

At the day of the colonoscopy an informed consent must be signed by the participants before inclusion into the project; specifically, the study participants also sign that they allow access to health and pathology files according to the Danish Health Act §43,1-3. An interview will be conducted to obtain personal and possible concurrent disease data, followed by blood collection prior to colonoscopy.

Blood samples of 90 mL will be collected from an antecubital vein with light stasis and subsequently handled and stored according to a validated standard operating procedure including pre-analytical and analytical aspects such as blood sampling, handling, storage, and the effects of freeze/thaw on biomarkers of interest (Multimedia Appendix 1). Specifically, the blood samples for plasma are centrifuged twice to reduce the contaminating effects of leucocyte- and platelet-derived granule proteins. All collection and storage tubes are marked with unique barcodes, which by 8 digits identify the hospital where the sample is collected (2 digits), identification of the subject (4 digits), and identification of the specific tube content (2 digits; serum, plasma or buffy-coat). The Freezer Works PC-based storage handling system is used to track every sample in the -80^o^C freezers, which are electronically surveyed and monitored 24 hours a day, 7 days a week.

Data including findings and interventions at colonoscopy will be registered in a locked Web-based database and continuous audit of the database will be performed ensuring correct data recordings. At the end of the study on-site audit sessions will be performed as well.

The FIT-negative participants are arbitrarily selected from the database of the Danish CRC Screening Program and will be invited to blood collection at the nearest participating hospital. The inclusion started August 2014 and is planned to terminate by late August 2016. A total of 6000 participants will be recruited. The informed consent, data collection, and blood collection, handling, and storage will be carried out according to the procedure for the FIT-positive participants.

The emerging results from the Endoscopy II Project will be used to identify the specific biomarker profile subsequently used in analyzing data for Part 1 of the Endoscopy III Project. The analysis will be carried out as shown in Table 1.

### Part 2

Limitations of FIT screening include suboptimal sensitivity that leads to false negative results, and thereby some participants with CRC or high-risk or medium-risk adenomas (Textbox 1) are not identified.

Due to the prolonged implementation of FIT screening in Denmark, the period between the first and second screening rounds is estimated to be 4 years; limited colonoscopy capacity will, however, extend the implementation period to about 5 years. Therefore, even low-risk adenoma participants, who far from always are identified by the FIT test, may develop either high-risk/medium-risk adenoma or even early CRC in that prolonged period. Therefore, Part 2 of the Endoscopy III protocol, initiated in March 2016, will include blood samples and data from 30,000 participants screened negative by the FIT testing. The 10 participating hospitals have the capacity to include these participants within 24 to 30 months. Similar to Part 1 FIT-negatives (hgb<100 ng/mL; OC-Sensor platform) the participants are identified and arbitrarily selected from the database of the Danish CRC Screening Program and will be invited to blood collection at the nearest participating hospital. Informed consent, data collection, and blood collection, handling, and storage will be carried out according to the procedure for Part 1 of the project.

At inclusion the participants accept to have blood and data collections after 2 and 4 years, respectively. The third blood and data collection will be approximated to the period just after the second FIT screening testing. All participants will be advised by electronic mail (e-boks in Denmark) 1 month before data and blood collections after 2 and 4 years, respectively.

**Table 1 table1:** Determination of the following biomarkers is in progress or planned in samples from the Endoscopy II Project with national and international academic and biotech laboratories.

Biomarker	Technique or platform
Profile of 8-15 plasma proteins	The Architect Automated platform, Abbott, Chicago, IL, USA
Soluble urokinase plasminogen activator receptor-I (suPAR-I), suPAR-II, suPAR-III, total suPAR	In-house ELISA platforms, Finsen Laboratory, Copenhagen, Denmark
Galectin ligands	In-house ELISA platforms, MD Anderson Cancer Center, Houston, TX, USA
Cathepsins	In-house ELISA platforms, University of Slovenia, Ljubljana, Slovenia
Cell-free DNA	inhouse PCR Platform, Roskilde Hospital, Roskilde, Denmark
Cell-free, tumor-derived DNA	Platform under development, Skejby Hospital, Skejby, Denmark
Nucleosomes	Tecan-based in-house ELISA platforms, Volition, Namur, Belgium
Proteomes	Mass-spectrometry-based platform, primarily tandem LCMS, Applied Proteomics Inc., San Diego, CA, USA
Metabolomes	Raman Hyperspectral Imaging, ChemImage INC., Pittsburg, PA,USA
YKL-40	Manual commercially available ELISA platform, Herlev Hospital, Herlev, Denmark
Profile of 4 soluble coagulation proteins	Luminex platform, Fred Hutchinson Cancer Research Center, Seattle, WA, USA
Nuclear magnetic resonance (NMR)	NMR profiles, University of Copenhagen, Copenhagen, Denmark
Gas chromatography-mass spectrometry (GC-MS)	GC-MS profiles, University of Copenhagen, Copenhagen, Denmark

Categories of the identified adenomas.Adenoma characteristicsHigh-risk adenomaLesion ≥ 20 mm or≥ 4 lesions orResection by piece-mealMedium-risk adenomaLesion ≥ 10 mm, but ≤ 20 mm or3-4 lesions independent of size orTubulovillous or villous lesion orHigh-grade neoplasiaLow-risk adenoma< 3 lesions (< 10 mm) orTubular lesion orLow-grade neoplasia

### Parts 1 and 2

Intensified follow-up of all included participants will be performed electronically via existing health databases and/or participant-specific health files using the unique 10-digit computerized Central Personal Registration number given to all Danish citizens. Thereby no-one is lost to follow-up. Among the aims are evaluations of the risk of developing intra-bowel as well as extra-bowel neoplasia among those diagnosed with adenomas, other benign bowel lesions, and those without any lesions in relation to the biomarkers determined in the project. It has previously been indicated that blood-based biomarkers may be useful to identify such at risk participants [23]. Specifically, the 30,000 FIT-negative participants will be followed-up according to the same aims to identify those with presence of bowel neoplasia although the FIT result was <100 ng/mL and those at risk of developing interval bowel neoplasia during the 4 to 5 years between the two first screening rounds.

Based on a number of approved addendums to the protocol the exact FIT hemoglobin concentrations will, among other parameters, be included for everyone participating in the project. Thereby combinations of blood- and feces-based screening platforms may improve the entire screening concept [24]. Among the aims is the ability to evaluate associations between hemoglobin concentrations and CRC or high-risk adenoma, medium risk-adenoma, low-risk adenoma, non-neoplastic bowel lesions or clean colorectum. Thereby, the amount of screen colonoscopies may be reduced significantly and independently of the cut-point hgb level of 100 ng/mL restricted to those who are in urgent need.

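### In Part 2 the second FIT is the only systematic route to colonoscopy, so FIT-missed and interval neoplasia are verified selectively and accuracy estimates will depend on the mix of detection routes

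*Protocol article*

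**What the plan says.** All statements are in the protocol article.

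- **Targets.** Methods (Parts 1 and 2) gives the 30,000 FIT-negative participants two aims: "to identify those with presence of bowel neoplasia although the FIT result was <100 ng/mL", and to identify "those at risk of developing interval bowel neoplasia during the 4 to 5 years between the two first screening rounds". Methods (Part 2) explains that participants with low-risk adenoma "may develop either high-risk/medium-risk adenoma or even early CRC in that prolonged period". The Abstract's conclusions list, among the purposes of the whole study, "to identify false negative participants, to identify participants at risk of interval neoplastic lesions".
- **Access to colonoscopy.** Methods (Part 1) describes the programme as "outreach FIT and subsequent offer of colonoscopy to participants with positive test results". No study colonoscopy is described for FIT-negative participants in either part.
- **Follow-up.** It is "performed electronically via existing health databases and/or participant-specific health files". In Part 2, "The third blood and data collection will be approximated to the period just after the second FIT screening testing".
- **Analysis.** Statistical Analysis makes CRC the primary endpoint and high-risk adenomas a secondary one, with emphasis on sensitivity, specificity and predictive value. It gives no sample size calculation for the 30,000 but presumes that the number suffices for the same calculations.
- **Reference standard.** The Discussion says that FIT and RAE will be compared in the FIT-positive and in the FIT-negative cohort, with colonoscopy as the gold standard.
- **Definition.** The Introduction defines interval cancer as "CRC diagnosed in the timeframe between screening rounds mostly due to false negative FIT results". Interval neoplasia, which would include adenomas, is not defined.

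**The concern.** Register linkage makes the follow-up of diagnoses complete, but it does not establish who has a lesion. An adenoma or early cancer without symptoms enters the record only if someone looks for it, and in this cohort the one systematic occasion to look is a positive second FIT. Verification therefore depends on FIT, the test against which the blood model is to be judged.

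Two consequences follow. First, if between-round diagnoses and second-FIT findings are analysed together, a blood model that mainly anticipates the next positive FIT could appear to predict interval neoplasia. Second, if participants without colonoscopy are counted as lesion-free, a marker that detects lesions missed by both FITs would be scored as giving false positives. Both bear on the aims of finding false negatives and those at interval risk.

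**Working it through.** **1. What the plan states.** No Part 2 case count and no split by route is given, so there is no plan figure to reproduce on this point. Statistical Analysis does give Part 1 yields per 8,000 FIT-positive participants:
- CRC: 450/8,000 = 5.6% to 500/8,000 = 6.25%.
- Adenomas: 2,200/8,000 = 27.5% to 2,500/8,000 = 31.25%.

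The Introduction gives FIT compliance of 33% to 64%.

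**2. Assumptions not in the documents.**
- Second-round uptake up to 90%, and positivity 3–7%.
- Colonoscopy completion 80–100% (adenoma calculation; 100% for CRC).
- CRC yield after a positive second FIT possibly as low as 3%; otherwise the Part 1 yields carry over.
- Between-round clinical colonoscopy 0.25–2% per year over 4.5 years (midpoint of 4 to 5), with adenoma yield 15–25%.
- Interval CRC 0.5–3 per 1,000.

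**3. Formulas.**
- Second-FIT cases = 30,000 × uptake × positivity × completion × yield.
- Between-round adenomas = 30,000 × annual rate × 4.5 × yield.
- Between-round CRC = 30,000 × interval risk.
- Share = second-FIT cases / (second-FIT + between-round cases).

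**4. Results.**

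| | Second FIT | Between rounds | Second-FIT share |
|---|---|---|---|
| Adenoma, lowest | 30,000 × 0.33 × 0.03 × 0.8 × 0.275 = 65 | 30,000 × 0.02 × 4.5 × 0.25 = 675 | 9% |
| Adenoma, middle | 30,000 × 0.64 × 0.05 × 0.275 = 264 | 30,000 × 0.01 × 4.5 × 0.20 = 270 | 49% |
| Adenoma, highest | 30,000 × 0.90 × 0.07 × 0.3125 = 591 | 30,000 × 0.0025 × 4.5 × 0.15 = 51 | 92% |
| CRC, lowest | 30,000 × 0.33 × 0.03 × 0.03 = 9 | 30,000 × 0.003 = 90 | 9% |
| CRC, middle | 30,000 × 0.64 × 0.05 × 0.05625 = 54 | 30,000 × 0.001 = 30 | 64% |
| CRC, highest | 30,000 × 0.90 × 0.07 × 0.0625 = 118 | 30,000 × 0.0005 = 15 | 89% |

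The share exceeds one half in about 54% of the adenoma scenarios and 47% of the CRC scenarios. These are counts of input combinations, not probabilities. At the middle second-FIT inputs, break-even lies at about 1.0% clinical colonoscopies per year (20% yield) and 1.8 interval CRC per 1,000.

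**5. How many are verified at all.** Middle case: 30,000 × 0.64 × 0.05 = 960 through the second FIT plus 30,000 × 0.01 × 4.5 = 1,350 otherwise, so 2,310 or 7.7% of the cohort. The extremes are 238 + 338 = 576 (1.9%) and 1,890 + 2,700 = 4,590 (15.3%). Overlap between the routes is ignored; it would lower these figures. At least about 85% would have no colonoscopy.

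**6. Effect on a pooled sensitivity.** Suppose, purely for illustration, that RAE detects 70% of second-FIT lesions and 40% of between-round lesions. Then pooled sensitivity = 0.40 + 0.30 × share, which is 43% at a share of 9% and 68% at 92%. The markers are the same throughout; only the route mix changes.

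**The case against.** The strongest reply is that this is detail for the full protocol or analysis plan: a case rule by date and route is one derived variable, and CRC and adenoma are already separate endpoints. That stands as far as the missing rule goes. It does not answer the Discussion, which states a colonoscopy reference standard for a cohort that is offered none. Nor does it answer Parts 1 and 2, which relates hemoglobin to bowel findings, including a clean bowel, after saying that hemoglobin will be recorded for every participant.

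Several stronger readings are tempting, and the documents do not support them:

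- **That most Part 2 cases will be FIT-detected.** With 64% uptake, 3–7% positivity and 90% attendance there are 518–1,210 colonoscopies. At a combined yield of 33.1–37.5% that gives 172–454 lesions; against an assumed 60 interval CRC the share is 74–88%. But this sets CRC plus all adenomas against CRC alone and puts between-round adenomas at zero. Like for like, second-round CRC is 518 × 5.6% = 29 to 1,210 × 6.25% = 76 against 60, or 33–56%. Health records also capture symptomatic and incidental diagnoses.
- **That the plan contradicts its own definition.** The Introduction defines interval cancer only. The Methods wording concerns lesions developing between rounds, which a lesion found at the second FIT can satisfy.
- **That second-round lesions are the opposite of FIT-missed.** A lesion present at the index test and found at the second FIT was missed by the first, which is the first Part 2 aim.
- **That the plan pools CRC and adenoma, or scores unverified participants as lesion-free.** No section says either. The timing of the third sample sets no case definition.

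**Conclusion.** The concern holds in a limited form. For the 30,000, lesion status is verified selectively and in dependence on FIT, and lesions negative on both FITs stay largely unseen. Colonoscopy therefore cannot serve as the reference standard for FIT-negative participants as a whole. Because the two detection routes are not separated, sensitivity and specificity would reflect the route mix as well as marker performance.

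The structural conclusion rests on the text. Its size does not: the second-FIT share of about 9–92% (adenomas) or 9–89% (CRC) rests on assumed uptake, positivity, yields and between-round diagnosis rates. The 43–68% range for pooled sensitivity also rests on an invented 70/40 split and shows only how far the mix could move the result. This is a worthwhile, low-cost improvement and no ground for calling Part 2 invalid.

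**What to change.** 1. Report CRC diagnosed after the index negative FIT and before the second FIT result (interval CRC) separately from CRC and adenoma found through the second FIT.
2. Describe second-round lesions as next-round detection. They may include first-FIT misses, but they cannot show that blood markers find what repeat FIT does not.
3. Treat adenoma status without colonoscopy as unknown, not lesion-free. Limit adenoma accuracy estimates to those with colonoscopy, with index hemoglobin in the model, and present them as conditional on that selection. Methods (Parts 1 and 2) already provides for exact hemoglobin values for everyone.
4. Reword the Discussion's statement on the reference standard so that it does not extend to the FIT-negative cohort as a whole.

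The cost is some wording and a derived variable from dates and diagnoses in records already linked. The downside is fewer cases per outcome and wider confidence intervals.
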